## Abstract

**Background:**

Children living in low and middle-income countries (LMICs) are at greater risk for experiencing adversities that can undermine their health and early development. Recently launched digital early childhood development (ECD) programs attempt to support families with young children in their home environments using digital technologies. However, relatively little is known regarding the effectiveness of these new technologies.

**Objective:**

The goal of this study is to rigorously assess the reach, effectiveness, and cost-effectiveness of a newly developed digital ECD platform called Afini. The Afini platform was designed to support parents of young children in low-resource settings to improve ECD and interact with caregivers through messenger services and a chatbot.

**Methods:**

This is a 3-arm cluster randomized controlled trial. In total, 2471 caregivers and their 3- to 9-month-old children were enrolled in the study across 164 study clusters in the San Marcos, Cajabamba, and Cajamarca provinces of Peru. Clusters of participants were randomly assigned to 1 of 3 groups: a control group (72 community clusters and 980 caregiver-child dyads), a home visit intervention group (20 community clusters and 316 caregiver-child dyads), and an Afini intervention group (72 community clusters and 1175 caregiver-child dyads). Families in the control group receive no focused ECD intervention. The home visit group is receiving biweekly home visits by a trained field staff following the national ECD program (*Programa Nacional Cuna Más*) curriculum and training guidelines. Caregivers in the Afini group are receiving ECD activities and advice through the digital platform. The primary study outcome is children’s overall development at the age of 2.5 years, using the internationally validated long form of the Global Scales for Early Development. Secondary outcomes include caregiver engagement; caregiver mental health; screen time; as well as caregiver reports of children’s motor, cognitive, language, and socioemotional development measured through locally piloted and validated tools.

**Results:**

Enrollment started in September 2021 and ended in March 2023. Endline assessments will take place between August 2023 and September 2024.

**Conclusions:**

This study is, to our knowledge, the first to rigorously assess the effectiveness and cost-effectiveness of digital ECD technologies in LMICs. Given the large number of children in LMICs currently receiving only limited external support, the evaluated platform has the potential to improve the short- and long-term well-being of millions of children and their parents globally.

**Trial Registration:**

ClinicalTrials.gov NCT05202106; https://clinicaltrials.gov/ct2/show/NCT05202106

**International Registered Report Identifier (IRRID):**

DERR1-10.2196/50371

## Introduction

According to the World Health Organization, early life adversity affects more than 250 million children younger than 5 years, making it more difficult for them to reach their developmental potential [1,2]. Chronic poverty, malnutrition, and high exposure to infectious diseases undermine children’s development in their early years [1] and limit their physical and cognitive development over time. The most recent estimates suggest that 30% of children younger than 5 years in low and middle-income countries (LMICs) are stunted [3], and 37% of children aged 3-4 years display deficits in their cognitive or socioemotional development [4]. Interventions targeted at this early life stage are crucial for creating environments that support healthy development [5-8] and ensuring children’s long-term economic and overall well-being [9].

Home visiting programs have emerged as one of the most promising and popular approaches for improving child health and well-being in both high- and low-income settings [10], with successful implementation in Bangladesh [11], Brazil [12], Colombia [13], Jamaica [14,15], Pakistan [16], Peru [17], and South Africa [18]. These programs involve training community agents on child development and having them meet with mothers or parents weekly, biweekly, or monthly to discuss their children’s overall well-being. They provide practical guidance to caregivers on creating a healthy and developmentally stimulating environment in the home. Home visiting programs usually have a structured curriculum containing essential child health and development topics that are covered during each home visit. Despite consistently positive impacts on maternal [19,20] and child well-being [21,22], most countries have not adopted home visiting programs at scale due to the high cost and logistical efforts associated with them. In Peru, the state-run national early childhood development (ECD) program (*Programa Nacional Cuna Más* [PNCM]) provides a crèche-based intervention in urban and periurban settings and traditional home visits by trained agents in rural settings [17,23,24].

The rapid rise in cell phone coverage globally [25] and the introduction of mobile computing devices such as smartphones and tablets have created new opportunities for health and social systems to engage with patients and parents at scale [26-28], resulting in a rapid growth in the development of software apps for these platforms [29-34]. Additionally, new mobile phone contracts that offer low-income families access to basic messaging software (such as WhatsApp and Facebook messengers) without formal data contracts have also contributed to the expansion. Such light messenger-only data plans allow users to share information, pictures, and videos on messaging platforms without incurring any cost per message or upload. In our pilot study, 84.4% (152/180) of families owned a smartphone and 94% (169/180) had internet connectivity at home [35]. In this setting, new artificial intelligence (AI)–based ECD technologies using automated chatbots to interact with caregivers of young children seem to be a potentially attractive new option to support parents and their children.

In this project, we will test whether one of these newly developed digital platforms, called Afini [36], can be effective at improving children’s development in a remote population in high-altitude rural Andean Peru. Through this study, we wish to assess the reach, impact, and scalability of the newly developed Afini platform as a tool for improving children’s early development; the subaims are to (1) improve the functionality and usefulness of the Afini platform through qualitative and quantitative feedback and to integrate of state-of-the-art machine learning algorithms, (2) assess the cost and cost-effectiveness of Afini platform as a tool, and (3) disseminate the findings to our targeted population and reach out to the policy makers for further scalability of digital platform initiatives on ECD.

## Methods

### Study Setting

The study is conducted in 3 provinces of the Cajamarca region (San Marcos, Cajabamba, and Cajamarca) in the Northern Andes of Peru. The altitude in the study area ranges between 1900 and 3900 m above sea level. The region is predominantly rural and has a large share of low-resource and remote households engaged in farming, making it representative of many rural and periurban settings in Andean South America. The majority (80%) have regular access to social media platforms [35]. Communities were classified in accordance with the Peruvian National Institute of Statistics and Informatics as urban (communities with >2000 inhabitants with contiguous and grouped homes forming streets) or rural (scattered or grouped houses of up to 2000 inhabitants per community [37]). The study area is partially covered by PNCM.

### Study Design

The study was designed and adapted based on a field-testing phase completed over a period of 5 months from February to July 2021. During the test phase, we conducted a mixed method feasibility pilot to test the reach, reception, and use of the Afini parenting platform. Specifically, we (1) systematically assessed internet connectivity in the greater study region, (2) conducted focus groups and in-depth interviews to adapt Afini to the local cultural context, and (3) assessed use over time and satisfaction with Afini in a sample of 280 mothers with children up to 2 years of age and smartphone access [35].

The study was designed as a 3-arm parallel cluster randomized controlled trial to assess the Afini platform’s effectiveness in improving ECD outcomes relative to a control group receiving no additional intervention as well as relative to a home visit group receiving an ECD home stimulation intervention (gold standard). The trial enrolled 2471 caregivers and their 3- to 9-month-old children across 164 community clusters from September 2021 to March 2023. As described above, communities were randomly assigned to the three study groups: (1) a control group receiving no additional ECD support (72 community clusters and 980 caregiver-child dyads), (2) a home visit intervention group receiving a biweekly home visit by a trained field staff following the national ECD program PNCM curriculum and training guidelines (20 community clusters and 316 caregiver-child dyads), and (3) the Afini intervention group receiving ECD activities and advice through the digital Afini platform (72 community clusters and 1175 caregiver-child dyads).

### Description of the Study Groups and Intervention

#### Control Group

The control group comprises families that receive the regular level of mother and newborn child health care in the region. They have not been benefitting from any ECD program or intervention, but they may have sought assistance regarding parenting from within their network. This study group is only visited once at the beginning (baseline survey) and once at the end of the study (endline survey and assessment).

#### Home Visit Intervention Group

Home visits are considered the gold standard for enhancing child health and development in LMICs [21]. Families in the home visit intervention group (home visit group) receive support through biweekly home visits following the nationally developed and validated curriculum of the national ECD program PNCM. The PNCM program offers home visits to low-income families residing in rural areas (*Servicio de Acompañamiento a Familias*) and daycare services in urban settings (*Servicio de Cuidado Diurno*) [23]. Specifically, all families in the home visit group are receiving biweekly home visits by our trained field staff from when their children turn 6 months until endline assessments at approximately 2.5 years of age. Trained staff members visit families at home every 2 weeks. During these visits, they follow a structured (age-specific) curriculum to educate parents on engaging in educational activities and games for daily interaction with their children, actively play with the child, and provide parents with a set of age-appropriate toys every 3 months. The toys and activities were designed in Peru to promote their children’s psychomotor, cognitive, language, and socioemotional development.

#### Afini Intervention Group

Caregivers in the Afini intervention group (Afini group) were introduced to the Afini digital system on Facebook Messenger during the study baseline visit. During the initial setup, families registered the child’s day of birth and other demographics for Afini to recommend a first educational activity.

After this initial visit, caregivers received automated weekly alerts with personalized content from Afini over Facebook Messenger. Specifically, the Afini system sent weekly reminders to engage in age-specific, health- and development-promoting activities as well as general information on child development and the child's progress. Afini was available for families 24/7, and families could request up to 4 personalized educational activities for their child, ask for advice, or ask any questions related to child development to the Afini chatbot system at any time. The personalization of content works based on the child’s age, initial child development assessment on the platform, and user preferences (ratings) for each educational content.

After approximately 1 year, caregivers in the Afini group will receive a short home visit to ensure they can still connect to the system. Caregivers continue to use Afini independently until they are visited at the end of the study (endline survey and assessment).

The Afini platform is a digital parental support platform for children younger than 5 years in LMIC settings. The platform can be accessed via Facebook Messenger, WhatsApp, or an independent Afini app. Once connected, the Afini content recommender system uses AI to learn about individual children’s needs and recommends content or ideas for activities that caregivers can practice at home together with their child. The platform tracks child development and caregivers can contact the assistant chatbots at any time to receive general advice on child development and parenting. Afini offers over 1500 age-specific, health- and development-promoting activities, articles, and tips to caregivers. Afini’s educational activities, tips, and content are designed in a fun, simple way and with materials that are commonly found at home. All Afini contents offered to caregivers in the Afini group were developed by early development experts and revised by local experts in Cajamarca [35].

### Ancillary Studies

In order to assess whether the usage and impact of Afini can be improved through incentives, a total of 20 study clusters among the 72 Afini intervention clusters were randomly selected for additional top-up intervention. Within these 20 clusters, all caregivers with a prepaid phone plan with either Claro or Bite phone operators were eligible to receive small biweekly data credit transfers with a value of between US $0.8 and US $2. The credit transfers can be used for unlimited access to WhatsApp and Facebook Messenger for 1-3 days, depending on the provider; the monetary value of US $2 corresponds to half a kilo of chicken at a local market. We will assess the marginal impact on the use and development of these incentives as well as their relative cost-effectiveness.

In addition, and to increase the generalizability across the country, we added a comparison group composed of families participating in the existing governmental PNCM program. These families were screened during the enrollment of the main trial and excluded due to their participation in another ECD program; they became eligible for the ancillary study. This PNCM comparison group comprises 237 caregiver-child dyads and is treated the same as a natural control group without intervention. This group was not randomly selected or assigned and will thus mostly be used for descriptive purposes and to provide further context for this study. In summary, the project thus included 2471 trial participants and 237 comparison group participants, totaling 2708 project participants.

### Sample Size Calculations

The study is powered to detect a 0.25 SD difference in normalized child development *z* scores (mean 0, SD 1) at the age 2 years between the Afini group and the control group and a difference of 0.5 SD in *z* scores between the home visit group and the control group. These calculations are based on the following assumptions: (1) an average of 15 (SD 5) children per village or study cluster, (2) an intraclass correlation of 0.12, (3) α=.05, and (4) an attrition rate of 15%. The estimated normalized effect size of 0.5 SD was based on 2 recent reviews of ECD home visiting programs [10,16]. We conservatively anticipate the Afini platform to only reach about half the target population and, thus expect an intention-to-treat effect size of 0.25 SD. Our assumptions regarding intraclass correlations, number of children per cluster, and attrition rates are based on a recently completed ECD-focused study in the same area [17].

### Recruitment

Recruitment occurred continuously over 18 months with a target to enroll 2460 caregiver-child dyads. To identify potential children, the local health facilities’ birth registries from San Marcos, Cajamarca, and Cajabamba were used. All children between 3 and 9 months of age identified during the recruitment period in the study catchment area were eligible. All families that complied with the eligibility criteria were visited in person by study staff and invited to participate. The only reasons for exclusion were if the (1) caregiver and child intended to migrate outside the study area within the next 12 months, (2) child had a diagnosis of congenital abnormalities or a disability such as deafness or blindness (as reported by the caregiver), and (3) child already participated in the national PNCM program and did not belong to the PNCM comparison group. The study was built on a long-standing relationship of the research team with the regional and local health centers that facilitated recruitment.

### Randomization Process

Stratified constrained randomization was used to ensure both spatial and covariate balance across groups. As study strata, 3 study provinces (Cajamarca, Cajabamba, and San Marcos) were used. Within each stratum, communities were allocated with ratios 3.6:1:3.6 for the control group, home visit group, and the Afini group, resulting in a final sample of 72 clusters in both the control group and Afini group and 20 clusters in the home visit group. A total of 1000 potential cluster allocations were randomly drawn using the Stata SE (version 16.0; Stata Corp) software package. We then chose the allocation minimizing mean differences across the 3 arms concerning variables such as cluster population size, cluster number of births, cluster altitude, household cell phone ownership, education of caregiver, and household wealth. Information on these covariates was obtained from governmental sources and validated by our field staff.

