## Results

As shown in Table 2, enrollment and baseline data collection were completed in March 2023, and endline assessments were launched in September 2023. Table 4 shows descriptive statistics for the baseline sample by study arm. On average, children were 5 months old at baseline, 49.9% (1223/2452) were female, 8.1% (199/2452) had low birthweight (<2500 g at birth), and 97.5% (2391/2452) of children had a child health card. On average, mothers were 28 years old and considered literate. Fathers were slightly older, with an average age of 31.5 years at baseline, and had slightly higher education levels than mothers. The average household consisted of 2.5 adults and 1 additional child (sibling).

**Table 4 table4:** Descriptive statistics.

Characteristics	Control (n=962)				Home visits (n=315)				Afini (n=1175)		
	Observations, n	Clusters, n	Mean (SE)	Observations, n		Clusters, n	Mean (SE)	Observations, n		Clusters, n	Mean (SE)
Child age (months)	959	67	5.0 (0.11)	315		19	5.1 (0.22)	1169		78	5.1 (0.10)
Child is female	954	67	0.51 (0.02)	314		19	0.48 (0.03)	1172		78	0.50 (0.01)
Child has a health card	959	67	0.98 (0.01)	315		19	0.97 (0.01)	1169		78	0.98 (0.01)
Child born <2500 g	949	67	0.08 (0.01)	308		19	0.10 (0.02)	1152		78	0.08 (0.01)
CREDI^a^ score	950	67	43.0 (0.066)	307		19	43.0 (0.163)	1163		78	43.2 (0.065)
Mother’s age (years)	945	67	27.7 (0.26)	311		19	28.6 (0.48)	1155		78	28.0 (0.22)
Mother is literate	941	67	0.98 (0.01)	307		19	0.97 (0.01)	1151		77	0.99 (0.004)
Mother education level	944	67	3.2 (0.08)	310		19	3.2 (0.23)	1154		78	3.4 (0.08)
Father’s age (years)	843	66	31.2 (0.26)	277		18	32.1 (0.52)	1027		76	31.6 (0.26)
Father is head of household	844	66	0.94 (0.01)	277		18	0.94 (0.02)	1026		76	0.94 (0.01)
Father education level	832	66	3.5 (0.07)	267		18	3.5 (0.22)	1007		76	3.7 (0.07)
SES^b^ index	957	67	2.9 (0.12)	315		19	3.1 (0.29)	1169		78	3.2 (0.12)
Stimulation index	868	66	3.4 (0.06)	285		19	3.4 (0.14)	1076		78	3.5 (0.06)

^a^CREDI: Caregiver Reported Early Development Instruments.

^b^SES: socioeconomic status.

We anticipate completing the endline assessments in September 2024 and presenting final trial results to the local and national governments in Peru in early 2025.

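### The clusters per arm in Table 4 (67/19/78) contradict the stated randomised allocation (72/20/72), and 19 enrolled dyads are missing from that table without explanation

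*Protocol article*

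**What the plan says.** Under Randomization Process, the article sets an allocation ratio of 3.6:1:3.6 for control, home visit and Afini within each province. It gives the outcome of that step as "resulting in a final sample of 72 clusters in both the control group and Afini group and 20 clusters in the home visit group". Study Design reports that "The trial enrolled 2471 caregivers and their 3- to 9-month-old children across 164 community clusters". It gives the arms as control ("72 community clusters and 980 caregiver-child dyads"), home visit ("20 community clusters and 316 caregiver-child dyads") and Afini ("72 community clusters and 1175 caregiver-child dyads"). The Abstract repeats these figures, and Ancillary Studies again puts the number of Afini clusters at 72.

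Table 4, in Results, describes the baseline sample by arm. Its column totals are 962 control, 315 home visit and 1175 Afini dyads. Its largest cluster counts are 67, 19 and 78.

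The Statistical Analysis section makes intention-to-treat the primary approach and uses cluster-robust standard errors. No section says that any cluster changed arm, and none explains the differences between Table 4 and the text.

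**The concern.** The number of clusters per arm is the basic fact of a cluster-randomised trial. The arm assigned to each cluster defines the intention-to-treat comparison, and the cluster is the unit on which the standard errors rest. Here the article gives two incompatible sets of counts. The difference is not one that ordinary attrition could produce, because one arm has gained clusters.

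If the arm variable behind Table 4 is also the one used for the outcome analysis, and it departs from the randomisation list, some clusters would be compared under an arm to which they were not randomised. The balance sought by the constrained randomisation would then no longer be assured. If Table 4 is right and the text is out of date, the reported allocation and ratio are wrong but the comparison itself may be sound. The reader cannot tell which case applies.

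The 19 dyads missing from the table's totals raise a smaller question of the same kind, because by column header they all come from the two arms other than Afini.

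**Working it through.** **1. The stated allocation is internally consistent.** The ratio terms sum to 3.6 + 1 + 3.6 = 8.2. Then 164 × 3.6/8.2 = 72, 164 × 1/8.2 = 20 and 164 × 3.6/8.2 = 72. At the planned 15 children per cluster (Sample Size Calculations), 164 × 15 = 2460, which is the target given under Recruitment. The enrolled dyads also add up: 980 + 316 + 1175 = 2471.

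**2. Text and Table 4 side by side.**

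| | Control | Home visit | Afini | Total |
|---|---|---|---|---|
| Clusters, text | 72 | 20 | 72 | 164 |
| Clusters, Table 4 (maximum) | 67 | 19 | 78 | 164 |
| Difference | −5 | −1 | +6 | 0 |
| Dyads, text | 980 | 316 | 1175 | 2471 |
| Dyads, Table 4 column totals | 962 | 315 | 1175 | 2452 |
| Difference | −18 | −1 | 0 | −19 |

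Table 4's ratio is 67/19 : 1 : 78/19 = 3.53 : 1 : 4.11, not 3.6 : 1 : 3.6.

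**3. Is it a single misprint?** No. Of the 13 rows, nine show 67 control clusters and nine show 78 Afini clusters. The lowest Afini count in any row is 76, still above 72.

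**4. Can empty clusters or missing values explain it?** They could take control from 72 to 67 and home visit from 20 to 19. They cannot add six clusters to Afini. The unchanged total of 164 is what a net difference in arm labels would produce.

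**5. Do the dyads move with the clusters?** Under the text's figures, control averages 980/72 = 13.6 dyads per cluster. If five control clusters had been relabelled between the text count and Table 4, control would lose about 5 × 13.6 = 68 dyads and Afini would gain dyads. In fact control falls by 18 and Afini does not change. The two sources therefore appear to group the children almost identically, and the conflict lies in the cluster counts attached to them.

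**6. The missing dyads.** The shortfall is 18/980 = 1.8% of control, 1/316 = 0.3% of home visit and 0% of Afini. The 2452 is not confined to the header: the percentages in the Results text use it as denominator.

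**7. Power.** The article states no power, so there is no figure to reproduce. Inputs from Sample Size Calculations are 15 children per cluster (SD 5, so CV = 1/3), ICC 0.12, α = .05 (two-sided assumed), 15% attrition, and effects of 0.25 SD (Afini) and 0.5 SD (home visit). With m = 15 × 0.85 = 12.75, the design effect is 1 + [(1 + CV²)m − 1] × ICC = 1 + (14.17 − 1) × 0.12 = 2.58. Dividing each arm's sample by 2.58 gives:

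- Afini against control: 91.5% with 72 and 72 clusters, 91.6% with 78 and 67.
- Home visit against control: 99.3% with 20 and 72 clusters, 99.0% with 19 and 67.

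**The case against.** The strongest reply is that this is a reporting inconsistency in a descriptive baseline table. The analysis plan already declares intention-to-treat, nothing says that outcomes will be grouped as in Table 4, and Afini has the same 1175 dyads under both cluster counts. That reply stands as far as it goes. It limits what can be claimed, but it leaves the contradiction in place.

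A reader might infer that six clusters were moved into Afini after randomisation and that the intention-to-treat grouping is therefore not the randomised one. The documents do not support this. An arm-coding error in Table 4 would give the same pattern, and so would a 72/20/72 that records the plan and not the final allocation. Communities split and merged after randomisation could also do so if the changes happened to offset. A switch already built into both sets of dyad counts cannot be excluded, but it is not shown.

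A reader might also point to cluster sizes: 13.6 control against 1175/72 = 16.3 Afini dyads under the text's counts, but 962/67 = 14.4 against 1175/78 = 15.1 under Table 4's. The second pair is closer. Any formal test of the first gap, however, rests on the planning SD of 5 instead of the observed spread, and on 72/72 being correct, which is the point in dispute. It establishes nothing about moved clusters or differential recruitment.

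Nor can one say that records were removed from the comparator arms only. The 18/1/0 split comes from column totals. No Afini row reaches 1175 (the largest is 1172), and absence from a baseline table does not mean exclusion from the endline analysis.

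**Conclusion.** The contradiction is certain: at least one set of cluster counts is wrong as written, by −5, −1 and +6 clusters across control, home visit and Afini. The documents do not show which set is wrong. The 19-dyad shortfall (0.8% of 2471) is also certain and unexplained.

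An intention-to-treat breach is one possible explanation among several. The effect on power is negligible on the protocol's own inputs, assuming a two-sided test. The point matters because the arm variable and the cluster identifier carry the whole randomised comparison, so it should be settled before the outcome analysis is run.

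**What to change.** - Check both sets of cluster counts against the randomisation list and correct whichever is wrong. If 67/19/78 was the true allocation, correct 72/20/72 and the 3.6:1:3.6 ratio wherever they appear. If 72/20/72 was, correct Table 4 and the arm coding behind it.
- State why Table 4 totals 2452 and not 2471, accounting for the 18 control dyads and 1 home visit dyad.
- Confirm in one sentence that the primary intention-to-treat analysis includes enrolled dyads by the arm to which their cluster was randomised. Any cluster that received a different arm's intervention is then treated as non-compliance and stays in its randomised arm.

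The cost is a check against the allocation file, a corrected table or text, and a sentence on the analysis grouping. No new data are needed.
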